## Abstract

**Background:**

The death of a partner is a critical life event in later life, which requires grief work as well as the development of a new perspective for the future. Cognitive behavioral web-based self-help interventions for coping with prolonged grief have established their efficacy in decreasing symptoms of grief, depression, and loneliness. However, no study has tested the efficacy for reducing grief after losses occurring less than 6 months ago and the role of self-tailoring of the content.

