**Objective:**

This study aims to evaluate the clinical efficacy and acceptance of a web-based self-help intervention to support the grief process of older adults who have lost their partner. It will compare the outcomes, adherence, and working alliance in a standardized format with those in a self-tailored delivery format and investigate the effects of age, time since loss, and severity of grief at baseline as predictors. Focus groups to understand user experience and a cost-effectiveness analysis will complement the study.

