### Main Research Hypotheses

The main research hypotheses include the following:

We hypothesize that the intervention will significantly decrease grief symptoms (primary outcome) as well as depression symptoms and perceived loneliness (secondary outcomes) compared with the control group.Considering that the self-tailored delivery format provides participants with the opportunity to meet their specific needs at any time, we hypothesize that the self-tailored intervention will lead to higher satisfaction with the intervention and to a higher decrease in grief, depression symptoms, and perceived loneliness than the standardized intervention.We hypothesize that the overall helpfulness of the modules, gains in mastery experiences, self-esteem, insights, the matching of the needs of the user (session outcomes), and a better working alliance mediate the effect of the treatment.Comparing the 2 active arms, we hypothesize that the self-tailored intervention will lead to better session ratings and a higher working alliance than the standardized intervention, thus leading to better outcomes after the intervention.

To better understand the intervention effects, exploratory analyses will test whether age, time since loss, and the severity of grief symptoms affect treatment outcomes. Technology acceptance and cost-effectiveness analysis are exploratory and have no a priori hypotheses.

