Multilevel mixed effects models with repeated measures data will be conducted to evaluate the efficacy of the intervention after 10 weeks and the stability of the effects after a further 10 weeks. Restricted maximum likelihood estimation will be used, which is recommended for small group samples and yields asymptotically efficient estimators for balanced and unbalanced designs. Mixed effects models have several advantages. These consider the dependency of the data and account for the correlation of the repeated measures within individuals. Furthermore, mixed effects models use all available data of each participant and estimate parameters of missing values. Models for each outcome variable will be computed. The pre-post comparisons of all outcome measures will include time as a within-group variable, the intervention format as a between-group variable, and an interaction term time by a group for cross-level interactions. To test the stability of the effects from the postintervention period to follow-up, only time will be included as a within-group factor in the mixed effects models. Cohen *d* will be calculated as effect size for all observed outcome variables. Furthermore, a Reliable Change Index will be computed as a measure of clinical change. Complementary analyses will test whether variables such as age, time since loss, and the severity of grief symptoms have an effect on the outcome by including them as predictors in the regression models. To analyze the longitudinal interplay of predictor variables and test mediation analyses, structural equation models will be conducted. Analyses will be conducted using SPSS Statistics (IBM) [58] and Mplus [59] software.

To explain technology acceptance, a backward regression analysis will be conducted. All qualitative data will be analyzed thematically, following the guidelines by Braun and Clarke [60], whereas reporting will be done according to the consolidated criteria for reporting qualitative research standards [61].

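### Age, time since loss and baseline grief are meant to explain the intervention effect, but the stated model adds them as predictors without a term that does so

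*Protocol article*

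**What the plan says.** The purpose is given in two places. Under Main Research Hypotheses: "To better understand the intervention effects, exploratory analyses will test whether age, time since loss, and the severity of grief symptoms affect treatment outcomes". The Study Paradigm section also says that the Swiss trial will explore what predicts the effect of the intervention. The Abstract's Objective is to "investigate the effects of age, time since loss, and severity of grief at baseline as predictors", which fixes grief severity as the baseline value.

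The Abstract's Background gives as part of the rationale that "no study has tested the efficacy for reducing grief after losses occurring less than 6 months ago", and Expected Findings lists support after a more recent loss first among the study's contributions. Under Participants, losses less than 1 month old are excluded and no upper limit is set, so recent and older losses are mixed in each trial.

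The method is in Statistical Analyses. "The pre-post comparisons of all outcome measures will include time as a within-group variable, the intervention format as a between-group variable", together with "an interaction term time by a group for cross-level interactions". For the three variables, it then tests whether they (the third being grief severity) matter, in these words: "the severity of grief symptoms have an effect on the outcome by including them as predictors in the regression models". The text states no product of these variables with group, with time, or with time by group, and no separate estimate for losses under 6 months.

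**The concern.** Whether an intervention effect depends on a patient characteristic is a question of moderation. In a model that holds baseline and week-10 scores as outcome rows, the effect is the time by group term, so moderation is the covariate by time by group term. A covariate added on its own answers a different question: are people with a higher covariate value more or less grieved on average, over both occasions and both arms? If recent loss goes with higher grief at entry, time since loss would appear as a predictor even if nobody responded to treatment.

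Two consequences follow. The reports could describe such a coefficient as evidence on who benefits, or on recent loss, when no described analysis supplies that evidence. And baseline grief, if entered in the grief model, predicts an outcome vector that already contains it, so it looks stronger than its relation to week-10 grief warrants.

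**Working it through.** The plan states no figure on this point, so there is none to reproduce. The check is of what the stated model estimates.

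**Inputs from the article (Sample Size):** allocation 35:35:15 in Switzerland (taken here as 70 pooled active against 15), 40:40 in Portugal and 20:20 in the Netherlands; expected effect above d = 0.80; probability level 0.05, assumed two-sided.

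**Assumptions, not in the article:** correlation rho between baseline and week 10; share p of losses under 6 months, 20-50%; complete data.

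**1. What the predictor coefficient measures.** Take no effect in early losses, a reduction of 0.8 SD in later losses, and p = 0.5.
- Time by group is the average effect: -(0.5 × 0 + 0.5 × 0.8) = -0.40.
- The early-minus-late coefficient is the 0.8 difference, halved because it exists at only one of two occasions, times the active share of the sample. At 40:40: 0.8 × 1/2 × 40/80 = 0.20. At 70:15: 0.8 × 1/2 × 70/85 = 0.33.

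A simulation of 4,000 trials per setting (rho = 0.6) agrees:

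| Allocation | Time by group, without / with predictor | Predictor coefficient (rejects) | Interaction coefficient (rejects) |
|---|---|---|---|
| 40:40 | -0.406 / -0.406 | 0.199 (16%) | 0.799 (49%) |
| 70:15 | -0.399 / -0.399 | 0.331 (39%) | 0.813 (34%) |

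Adding the predictor leaves time by group unchanged, so the absence of effect in early losses stays hidden. The predictor coefficient depends on the allocation ratio and is not the difference in effect. Only the interaction recovers 0.80.

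**2. Baseline grief in the grief model.** With equal variances, the slope of the baseline row on baseline grief is 1 and that of the week-10 row is rho. One common coefficient averages them: (1 + rho)/2.
- rho = 0: (1 + 0)/2 = 0.50, where the true week-10 slope is 0.
- rho = 0.5: 0.75, where the true slope is 0.50.
- rho = 0.6: 0.80, where the true slope is 0.60 (simulated 0.80 and 0.60).

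**3. Precision once the right term is used.** With the analysed score scaled to SD 1 (for a change score, rho = 0.5) and before dropout:
- SE of the difference in effect = sqrt[(1/n1 + 1/n0)(1/p + 1/(1-p))]
- Power for 0.8 = Φ(0.8/SE - 1.96)
- 95% CI half-width for early losses alone = 1.96 × sqrt[(1/n1 + 1/n0)/p]

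Portugal, p = 0.5: SE = sqrt(0.05 × 4) = 0.447; power = Φ(1.79 - 1.96) = 0.43. Netherlands, p = 0.2: SE = sqrt(0.10 × 6.25) = 0.791; power = Φ(1.01 - 1.96) = 0.17.

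| Trial | Power for 0.8 SD difference (p 0.2 to 0.5) | Difference detectable with 80% power (p 0.2 to 0.5) | CI half-width, early losses (p 0.2 to 0.5) |
|---|---|---|---|
| Switzerland | 20% to 29% | 1.99 to 1.59 SD | 1.25 to 0.79 SD |
| Portugal | 30% to 43% | 1.57 to 1.25 SD | 0.98 to 0.62 SD |
| Netherlands | 17% to 24% | 2.21 to 1.77 SD | 1.39 to 0.88 SD |

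The simulated rejection rates are somewhat higher than these because rho = 0.6 gives a change-score SD of sqrt(2 × 0.4) = 0.89.

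**The case against.** The best defence is that the article never says main effects only. The Study Paradigm section uses the word predictor for something that bears on the intervention's effect, so the authors may intend interactions, and a full analysis plan could spell them out. That is a fair caution about intent. It does not rescue the text: the section states one interaction, names the three variables next, and says how they enter. That is a stated method which misses its stated purpose, not an omitted detail. Reading predictor more loosely, as a predictor of change, would need covariate by time, which is not stated either.

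A reader might infer that the trials leave their headline question untested. The documents do not support this. Losses under 6 months are background rationale and a claimed contribution; they are in none of the research goals or main hypotheses. The main hypothesis is overall efficacy, which time by group tests, and the article already labels these analyses exploratory.

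A reader might also infer that the overlap of baseline grief with the outcome undermines the efficacy result. It does not. It arises only if baseline severity enters the stacked model. It concerns the grief outcome and not depression or loneliness, has no bearing on age or time since loss, and leaves time by group unbiased in complete data.

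Finally, the correct term will have wide intervals. That stands, and it is why the fix asks for estimates and not for a confirmatory test.

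**Conclusion.** The point holds as one of specification. The exploratory analyses are meant to explain the intervention effects, but the terms stated for them estimate neither moderation nor change, and no estimate is planned for losses under 6 months. In the worked case the coefficient is 0.20 (40:40) or 0.33 (70:15), against a true difference in effect of 0.80. In the grief model the severity coefficient is (1 + rho)/2 in place of rho, for example 0.80 in place of 0.60. These figures rest on assumed correlations, an assumed early-loss share and complete pre-post data; the form of the problem does not depend on them. The primary and secondary treatment comparisons are unaffected. The analysis should be corrected before the data are analysed, but it is not a flaw in the main test.

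**What to change.** Replace the sentence on the complementary analyses with wording to this effect: age, time since loss and baseline grief severity are examined as modifiers of the week-10 effect through covariate by group by time, or through covariate by group in a baseline-adjusted week-10 model. Baseline grief is used only as a covariate or moderator of post-baseline scores. The intervention effect is reported with a 95% CI for losses under 6 months and for 6 months or more.

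Keep the exploratory label, and state that precision will be low. Analysing time since loss on a log scale is optional.

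The cost is wording only. Age and time since loss are already listed as baseline context variables, and grief is measured at baseline in all three trials. No change to sample size or data collection is needed.

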### Sample Size

Sample size was determined by a power analysis based on a probability level of 0.05 and a power of 0.80 with G*Power [36], which is based on the results of the evaluation of LIVIA [14]. As in LIVIA, we expected a large effect size of Cohen *d*>0.80 for the decrease in grief as primary outcome, measured by the Texas Revised Inventory of Grief (TRIG), in the comparison of the intervention with a waitlist control group or care-as-usual control group. For the comparison of the standardized intervention with the self-tailored interventions, we expect a small to moderate effect (Cohen *d*=0.30) in favor of the self-tailored version. Power analyses for a repeated measures ANOVA with a within-between interaction for 3 groups in Switzerland estimated a sample size of at least 85 participants. For the 2-arm designs in Portugal and the Netherlands, we anticipate a dropout rate of 15% and, consequently, efforts will be made to recruit more primary end users than indicated by the power analysis.

For the target group of primary end users, older mourners, the aim is to include at least 85 participants in the study conducted in Switzerland with an allocation of 35:35:15 for the 2 active arms and the waitlist control group, respectively; at least 80 participants in Portugal with an allocation of 40:40; and at least 40 participants in the Netherlands, with an allocation of 20:20.

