### Randomization

All eligible participants are randomly assigned to the active arm of the study (including the 2 active arms, standardized or self-tailored intervention format for the trial in Switzerland) or to the control or care-as-usual groups, depending on the implementation country. Participants assigned to the active arms will receive a participant code that gives them access to the self-help program and will be asked to use it for 10 weeks. Participants in the waitlist control group will start using the program 10 weeks after randomization. In Portugal, participants in the care-as-usual group can use the program after 20 weeks of follow-up, if requested.

For the 3 trials, the block-wise randomization was performed by an external programmer not involved in the trial using a random allocation sequence. The trials are unblinded. In Switzerland, the participants register on the study website and fill out the baseline questionnaire. Then, a member of the study team conducts the screening telephone call and allocates the participants to the 3 arms based on randomization numbers provided by the external programmer. In the Netherlands and in Portugal, participants are directly contacted by the teams responsible for implementing the study. Contacts are made based on their own professional lists. In the 3 countries, participants receive the intervention link after their eligibility has been confirmed in a phone call or an individual interview, depending on the implementation country.

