#### Technology Acceptance

The trial conducted in the Netherlands is aimed at thoroughly investigating the technology acceptance of the intervention, specifically focusing on perceived usefulness (self-devised) and effort expectancy (based on the study by De Veer et al [52]), measured at baseline. The usability (based on the study by Holden [53]) and user experience using the AttrakDiff instrument (User Interface Design GmbH) [54] will be assessed midintervention. Finally, after the intervention (week 10), usability and user experience will be measured again, and participants will be asked to complete a measure of acceptance (self-devised) and effort (based on the study by De Veer et al [52]). In addition, at this phase, we will add open questions to assess the use and appreciation of mood self-check monitoring and respective feedback messages and critical incidents. As a follow-up, focus groups will be conducted to better understand the perceived benefit of the web-based self-help program. Focus groups will address usability and technical acceptance, answer which intervention elements need improvement, and assess the potential use of the intervention in daily and working routines.

The research team agreed to share all the materials used in the study, including the scales used (if open access) and the focus group scripts upon request to the corresponding author.

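### Backward elimination for technology acceptance in a small Dutch sample keeps chance predictors well above the nominal rate and inflates R²; a short prespecified model would be better

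*Protocol article*

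**What the plan says.** The Statistical Analyses section commits to a method: "To explain technology acceptance, a backward regression analysis will be conducted".

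The Technology Acceptance section describes the Dutch measures. The baseline focus is given as "specifically focusing on perceived usefulness (self-devised) and effort expectancy". Usability and user experience are assessed midway through the intervention. At week 10, "usability and user experience will be measured again, and participants will be asked to complete a measure of acceptance (self-devised) and effort". The section does not say which of these measures enter the regression.

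Sample Size sets the Dutch trial at "at least 40 participants in the Netherlands, with an allocation of 20:20". For the two-arm designs it adds "we anticipate a dropout rate of 15" per cent, and that "efforts will be made to recruit more primary end users than indicated by the power analysis". Under Randomization, "Participants in the waitlist control group will start using the program 10 weeks after randomization". The article does not say whether acceptance data from these later users join the regression.

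Main Research Hypotheses labels technology acceptance as exploratory, with no prior hypothesis.

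**The concern.** Backward elimination lets the data choose the predictors and then reports the survivors as though they had been fixed beforehand. With few participants and several candidates, two things follow. The chance that at least one unrelated candidate survives is well above the threshold used for each term. And the R² of the surviving model is too high, because the terms were kept for fitting this particular sample.

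Technology acceptance is the complementary research goal of the Dutch trial, and this regression is the only model named for it. A reader of the results could take the surviving terms as what drives acceptance among older mourners, and the R² as a measure of how well acceptance is understood. Both would be less secure than they looked.

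**Working it through.** The article gives no error rate, predictor count or sample size for this regression, so there is no stated figure to reproduce.

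**Number of users.** Active arm at the minimum: 20. After 15% dropout: 20 × 0.85 = 17. Both arms, if waitlist users contribute: 40, or 40 × 0.85 = 34.

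**Number of candidates.** With acceptance at week 10 as the outcome:
- Counting constructs gives 4: perceived usefulness, effort, usability and user experience.
- Counting each measurement gives 7: usefulness and effort expectancy at baseline (2), usability and user experience midway (2) and again at week 10 (2), and effort at week 10 (1).

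**Assumptions.** Removal at p ≥ 0.10 or p ≥ 0.05. Pairwise correlation between candidates of 0 or 0.5. Every candidate unrelated to acceptance, so that true R² = 0.

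**Rough check by formula.** If each of k unrelated, independent candidates survived with probability p, at least one would survive with probability 1 − (1 − p)^k:
- k = 4: 1 − 0.90⁴ = 0.34; 1 − 0.95⁴ = 0.19
- k = 7: 1 − 0.90⁷ = 0.52; 1 − 0.95⁷ = 0.30

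The sample size does not appear in this expression, so more users should barely lower the retention rate.

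**Simulation.** Backward elimination by ordinary least squares t tests, at least 3,000 runs per setting (Monte Carlo standard error at most √(0.25/3000) = 0.9 percentage points):

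| Candidates | Removal at | Any noise term kept, n = 17–20 | Any noise term kept, n = 34–40 | Mean R² if any kept, n = 17–20 | Mean R² if any kept, n = 34–40 |
|---|---|---|---|---|---|
| 4 | 0.05 | 19–21% | about 20% | 0.30–0.37 | 0.15–0.19 |
| 4 | 0.10 | 35–37% | 35–37% | 0.26–0.31 | 0.13–0.16 |
| 7 | 0.05 | 34–37% | about 33% | 0.34–0.42 | 0.16–0.21 |
| 7 | 0.10 | 57–61% | 55–57% | 0.32–0.39 | 0.15–0.20 |

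Going from 17–20 to 34–40 users leaves retention almost unchanged and roughly halves the apparent R².

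**When some candidates matter.** These runs use n = 20, candidate correlation 0.5 and assumed effect sizes. The share of kept predictors that were noise, over removal at 0.05 to 0.10, was:
- 4 candidates: 29–39% with one true predictor (standardized coefficient 0.5); 15–19% with two (0.4 each).
- 7 candidates: 54–61% with one true predictor (0.5); 34–41% with two; 23–27% with three (0.33 each).

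With seven candidates, one true predictor and removal at 0.10, the exact correct model was found in 31% of runs, and at least one false predictor was kept in 59%.

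**The case against.** Four points can fairly be made for the plan.

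First, a reader might infer that more than half of such analyses will select noise. The article does not support that as a general statement. It needs about six or seven candidates, removal at 0.10 and no real predictor among them. The Technology Acceptance section lists measures and time points without calling any of them predictors, and no threshold is given. An article may leave both to a fuller document, so their absence is not held against it.

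Second, a reader might infer that whatever the regression reports will be largely chance. Usability, user experience and effort are self-reported at the same time as acceptance, so some are likely to be related to it. With two or three true predictors, noise was the minority of what was kept in every setting tried.

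Third, a reader might think that redesign of the program rests on this regression, or that it is the only quantitative analysis. Study Paradigm and Technology Acceptance give the question of what to improve to focus groups, and Statistical Analyses also plans scale averages, two-way correlations and a check for multicollinearity.

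Fourth, the analysis is declared exploratory, and 40 is a minimum that may be exceeded.

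All four limit the size and importance of the problem. None removes it. The choice of backward elimination is stated in the article; a candidate list or threshold supplied elsewhere would change the magnitude, not the mechanism. The exploratory label lowers the strength of the claim but does not correct p values, intervals or R² computed as if nothing had been selected. A multicollinearity check does not address selection.

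**Conclusion.** The point holds in a conditional form. With about 17–20 users, and no candidate related to acceptance, backward elimination keeps at least one noise predictor in roughly 20–37% of runs for four candidates and 34–61% for seven. The kept model then shows a mean R² of about 0.26–0.42 where the truth is 0. If waitlist users bring the number to 34–40, retention stays about the same and the mean R² falls to about 0.13–0.21, still inflated.

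These figures rest on assumed removal thresholds of 0.05 and 0.10, on the two ways of counting candidates, and on the all-noise case, which calibrates the method and does not forecast the result. Real signal lowers the share of false findings but did not bring it near zero in any setting tried. The matter is a minor improvement to an exploratory analysis; the efficacy comparisons do not depend on it.

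**What to change.** In Statistical Analyses, replace the backward regression with one prespecified model: two or three theory-based predictors of week-10 acceptance, entered together and kept whatever their p values. Baseline perceived usefulness, baseline effort expectancy and week-10 usability would be one such set. State which Dutch users are included and, if waitlist users are, at which time point their acceptance is taken.

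Report coefficients with 95% confidence intervals and a bootstrap optimism-corrected R². The correction is needed even without selection: three unrelated predictors give an expected apparent R² of 3/(n − 1), which is 3/19 = 0.16 at n = 20 and 3/16 = 0.19 at n = 17. Report the remaining measures through the two-way correlations already planned, adding confidence intervals and making no selection by significance.

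The cost is a few sentences of analysis text and no new data. The price is fewer predictors in the model and a less favourable R².
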